#### Sample Size

A total study sample size of 240, with 120 each in the intervention and control arms, was estimated based on the estimates of diastolic blood pressure at baseline (mean 80.9, SD 10.9 mm Hg) and the postintervention time point (mean 75.4, SD 11.5 mm Hg) from a previous randomized controlled trial in Kerala [23]. *OpenEpi* was used for sample size calculation. The sample size was estimated at 80% power, a 95% CI, a 20% nonresponse rate, and a design effect of 1.5.

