#### Sampling

The study followed a multistage cluster sampling method. In the first stage, all taluks in the Kannur district were listed, and then 1 taluk (ie, Payyanur taluk) was selected. One rural (ie, Karivellur-Peralam gram panchayat) and one urban (ie, Payyanur municipality) administrative unit (cluster) from this taluk were then selected for the study (Figure 2). In stage 2, a door-to-door household survey will be conducted in these 2 rural and urban clusters. Household members aged 40 to 59 years will be screened for eligibility after consent is obtained. In the third stage, eligible participants (those with hypertension and access to WhatsApp) will be surveyed. After the baseline survey, the study’s recruitment will follow a nonrandomized approach (Figure 3) without matching or blinding as these are not applicable in this study setting. Upon recruitment and consent, the first participant will be allocated to the intervention group, and the next participant will be allocated to the control group. The participants will be recruited into the intervention and control groups sequentially in a 1:1 ratio. This process will be conducted iteratively until the sample size of 240 is reached (ie, 120 in the intervention group and 120 in the control group). At the cluster level, this amounts to 120 participants per cluster (urban and rural), with 60 of them in the intervention group and 60 in the control group.

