#### Statistical Analysis

The survey data collected will be entered into a Microsoft Excel spreadsheet and then exported to SPSS (version 26; IBM Corp) for coding and analysis. Codebooks and frequency tables will be generated to characterize the responses and identify any data entry errors. The missing data will be characterized as missing at random and missing not at random. The data missing at random will be addressed by creating a new variable or recoding an existing variable to account for the missing response. The data missing not at random will be addressed using the last observation carried forward approach (if the missing data were due to loss to follow-up) or regression imputation. Case deletion will be used if there are any missing data observed in multiple outcome variables. The analysis will be conducted adhering to the intention-to-treat approach. Study variables will be developed based on the operationalization plan shown in Table 1.

Descriptive analyses, including frequencies and percentages for categorical variables and means and SDs for continuous variables, will be conducted to understand the sample characteristics. The sociodemographic and health-related characteristics of the intervention and control groups will be compared at baseline. Furthermore, the outcome variables, including medication and lifestyle factors, will be compared between and within the intervention and control groups using baseline and follow-up data.

The comparison of categorical outcomes (medication and lifestyle factors) between and within the intervention and control groups will be conducted using the chi-square test and logistic regression. The regression analysis will be reported as unadjusted odds ratios with 95% CIs. The comparison of continuous outcomes (waist-to-hip ratio, awareness of hypertension, medication adherence score, and duration of physical activity) between the intervention and control groups will be conducted using a 2-tailed independent-sample *t* test (for normally distributed data) and the Mann-Whitney *U* test (for nonnormally distributed data). For comparisons of continuous outcomes within the intervention and control groups, a paired *t* test (for normally distributed data) and a Wilcoxon signed-rank test (for nonnormally distributed data) will be used.

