The generalized estimating equations model will be used to assess the effectiveness of the mHealth intervention based on the longitudinal study data (data from the baseline and follow-up surveys). Variables such as time, intervention, time-intervention interaction, and other sociodemographic factors will be considered in the model. The analysis using the generalized estimating equations model will be presented as adjusted odds ratios with 95% CIs. The significance will be considered at a *P* value of less than .05.

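### Household members can be enrolled together, but no named analysis recognises the household; under alternation this would make between-arm intervals somewhat too wide and any pooled intervals too narrow

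*Protocol article*

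**What the plan says.** The Sampling section states that "a door-to-door household survey will be conducted in these 2 rural and urban clusters", and that "Household members aged 40 to 59 years will be screened for eligibility after consent is obtained". Eligible people are then surveyed and recruited. No rule restricts enrolment to one person per household. Allocation is by individual and by order: "the first participant will be allocated to the intervention group, and the next participant will be allocated to the control group". It adds: "The participants will be recruited into the intervention and control groups sequentially in a 1:1 ratio". Each of the two areas, rural and urban, contributes 60 participants per arm.

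The Statistical Analysis section compares categorical medication and lifestyle outcomes by chi-square test and logistic regression. The comparison of continuous outcomes (waist-to-hip ratio, awareness, medication adherence score, duration of physical activity) "between the intervention and control groups will be conducted using a 2-tailed independent-sample" t test or the Mann-Whitney test. For effectiveness, "The generalized estimating equations model will be used to assess the effectiveness of the mHealth intervention based on the longitudinal study data". The data meant are the baseline and follow-up surveys; the terms listed are time, intervention, their interaction and sociodemographic factors.

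The Sample Size section applies a design effect of 1.5, and the Discussion says that the cluster effect was allowed for in the sample size.

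**The concern.** People aged 40 to 59 in one home are often couples. They tend to share meals, so salt, processed food, and fruit and vegetable intake are likely to be correlated within a home. Adherence to a healthy lifestyle is part of the primary outcome, and the prevalence of these dietary behaviours is secondary. The diet items, where categorical, fall under the chi-square test and logistic regression, which treat every participant as independent.

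The plan allows for correlated participants when it sets the sample size, but names no analysis that carries a cluster through to inference. At stake is the accuracy of the standard errors: lost precision for the comparison of arms, and overstated precision for any estimate that pools the arms.

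**Working it through.** **The plan's own figure.** The inputs from the Sample Size section are "diastolic blood pressure at baseline (mean 80.9, SD 10.9 mm Hg" and "the postintervention time point (mean 75.4, SD 11.5 mm Hg", a difference of 80.9 − 75.4 = 5.5 mm Hg, with 80% power. I take the 95% level as two-sided 5%.

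n per arm = (10.9² + 11.5²)(1.96 + 0.8416)² / 5.5² = 65.1, rounded up to 66. Then 66 × 1.5 × 1.2 = 118.8, so 119 per arm (238 in total), which agrees with the stated 120 (240). The sample size is not in dispute.

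**Household effect.** Let f be the share of participants enrolled together with one other household member, ρ the within-household correlation of the analysed quantity, s² its variance, and n the number per arm.

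- Pairs split across arms: there are fn pairs, so the two arm means have covariance fρs²/n. Var(difference) = 2s²/n − 2fρs²/n = (2s²/n)(1 − fρ). The naive formula omits the last factor.
- Both arms pooled: Var(mean) = (s²/2n)(1 + fρ).
- Actual type I error of a naive 5% test with split pairs = 2[1 − Φ(1.96/√(1 − fρ))].

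Neither f nor ρ is in the documents; the values below are assumptions.

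| f | ρ | 1 − fρ | Correct SE of arm difference, relative to naive | Type I error of naive 5% test | 1 + fρ | Correct pooled SE, relative to naive |
|---|---|---|---|---|---|---|
| 0.1 | 0.2 | 0.98 | 1.0% smaller | 0.0477 | 1.02 | 1.0% larger |
| 0.1 | 0.5 | 0.95 | 2.5% smaller | 0.0443 | 1.05 | 2.5% larger |
| 0.2 | 0.2 | 0.96 | 2.0% smaller | 0.0455 | 1.04 | 2.0% larger |
| 0.2 | 0.5 | 0.90 | 5.1% smaller | 0.0388 | 1.10 | 4.9% larger |
| 0.3 | 0.2 | 0.94 | 3.0% smaller | 0.0432 | 1.06 | 3.0% larger |
| 0.3 | 0.5 | 0.85 | 7.8% smaller | 0.0335 | 1.15 | 7.2% larger |

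**Simulation check** (240 participants, t test, 5,000 runs per setting). Strict alternation with household members recruited consecutively gave a type I error of 0.037 at f = 0.2, ρ = 0.5, against 0.039 by formula, and 0.023 at f = 0.5, ρ = 0.5, against 0.024 by formula. With household members spread at random over the arms, it stayed between 0.045 and 0.053 over all settings tried (f = 0.2 or 0.5, ρ = 0.5 or 0.8), which is essentially nominal.

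**The case against.** The strongest reply is that much of this rests on silence.

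- **The GEE.** A reader might infer that the GEE treats participants as independent. The article does not say so. It ties the model to the two surveys and leaves the subject unit and working correlation open, and a condensed article may leave those to a fuller plan. What stands is that no stated analysis names the household, and that the two-sample and chi-square tests, which are fixed in the text, cannot accommodate it.
- **Shared households.** The absence of a one-per-household rule does not show that couples were enrolled. Both members would have to be aged 40 to 59, hypertensive, with WhatsApp access, otherwise eligible and consenting. This stands, and the size is therefore conditional.
- **Direction.** A reader might infer inflated false positives, or intervals that are wrong in every case. Under the stated alternation, consecutive members are split and the arm comparison is conservative; if members are spread at random, it is near nominal. An anti-conservative arm comparison would need households kept in one arm, which is not this design.
- **Size.** Larger errors can be produced: f = 0.6 and ρ = 0.6 make the naive standard error 1/√0.64 = 1.25 times the correct one. Nothing in the documents supports such values. For the time-by-intervention term, ρ is the correlation of changes, and stable household similarity in diet largely cancels there.
- **Power.** On the plan's diastolic figures, 96 per arm (120 less 20%) gives about 92% power in an individual-level analysis, so a small loss of efficiency does not threaten that comparison.
- **Pooled percentages.** The Statistical Analysis section promises frequencies and percentages here, and mentions confidence intervals only for odds ratios. The pooled-interval point applies only if such intervals are reported.

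**Conclusion.** The point holds in a conditional and modest form. The sampling allows several participants per household, and no named analysis recognises this. If it happened and members were recruited consecutively, between-arm standard errors would be overstated and the tests conservative, while standard errors for pooled percentages would be understated. For assumed f of 0.1 to 0.3 and ρ of 0.2 to 0.5, the discrepancy is about 1% to 8% either way, and it is zero if no household contributed two people. It is not evidence that the trial would report false positive effects. It is worth correcting because the remedy is cheap and recruitment, now complete, can no longer be changed, while the analysis was expected to run to April 2026.

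**What to change.** - Attach a household identifier to each participant's identification number, and report the number of households with more than one participant and how their members fell across the arms.
- Define the household as the GEE cluster, with person and survey round within it, and use robust standard errors. Keep the rural/urban unit as a fixed term, because recruitment was fixed at 60 per arm in each.
- Take the between-arm inference, and any interval for pooled baseline percentages, from that model (with a link suited to each outcome) in place of the independent-sample tests.

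The cost is some data linkage, which the home-visit surveys should make possible, and a little analysis work; no new participants or visits are needed. If no household contributed two people, robust standard errors clustered by household equal those clustered by person, so nothing is lost. The change corrects the variance only. Where a household is split across arms, shared food or shared messages could still bias the comparison, and clustered standard errors do not cure that.

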#### Study Outcomes

The primary outcomes are the evaluation of the impact of the WhatsApp-led mHealth strategy on blood pressure measurements and adherence to medication and a healthy lifestyle in adults with hypertension aged between 40 and 59 years.

The secondary outcomes are the estimation of the prevalence and control of hypertension; percentage of participants adhering to antihypertensive medication; and prevalence of tobacco use, alcohol consumption, physical activity, diet patterns (such as frequency of fruit and vegetable consumption and processed food intake), and salt intake, as well as the estimation of digital literacy and the intention to use the mHealth strategy among adults with hypertension aged 40 to 59 years.

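### The effectiveness model is to be reported only as odds ratios, which do not fit mean diastolic blood pressure, the outcome the trial is sized on

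*Protocol article*

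**What the plan says.** All references are to the protocol article, quantitative phase.

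- **Study Outcomes:** "The primary outcomes are the evaluation of the impact of the WhatsApp-led mHealth strategy on blood pressure measurements", together with adherence to medication and lifestyle. Control of hypertension is listed separately, as a secondary outcome.
- **Sample Size:** the calculation is "based on the estimates of diastolic blood pressure at baseline (mean 80.9, SD 10.9 mm Hg) and the postintervention time point". The postintervention values are a mean of 75.4 and an SD of 11.5 mm Hg. The section adds: "The sample size was estimated at 80% power, a 95% CI, a 20% nonresponse rate, and a design effect of 1.5".
- **Statistical Analysis, simple comparisons:** categorical outcomes, described as medication and lifestyle factors, get a chi-square test and logistic regression with unadjusted odds ratios. The sentence on t tests and Mann-Whitney tests begins: "The comparison of continuous outcomes (waist-to-hip ratio, awareness of hypertension, medication adherence score, and duration of physical activity". These four variables complete the list. SBP and DBP are not in it.
- **Statistical Analysis, effectiveness:** a GEE on baseline and follow-up data, with time, intervention, their interaction and sociodemographic factors. The only statement of its effect measure is: "The analysis using the generalized estimating equations model will be presented as adjusted odds ratios with 95% CIs".

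**The concern.** The sizing, the primary outcome and the effectiveness analysis should concern the same quantity. Here the first two point to blood pressure as measured, and the third is stated on a scale that requires a categorical response.

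This matters more than it would in a randomized trial. Allocation is by alternation, so the adjusted model, not the unadjusted t test, carries the effectiveness claim. If its odds-ratio rule is followed, the plan gives no adjusted estimate of the blood pressure effect in mm Hg. If the rule is quietly dropped, the choice between a mean difference and some cut-point stays open for a primary outcome after the data are in. Data collection was completed in August 2025, so power lost to a categorical analysis cannot be regained by recruiting more participants.

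**Working it through.** **1. Is the trial sized on a difference in means?**

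Inputs from Sample Size: means 80.9 and 75.4, SDs 10.9 and 11.5, 80% power, 20% nonresponse, design effect 1.5. The 95% CI is taken as two-sided alpha 0.05.

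- Difference: 80.9 − 75.4 = 5.5 mm Hg.
- Pooled SD: √((10.9² + 11.5²)/2) = √125.53 = 11.20.
- n per arm = 2 × (1.960 + 0.842)² × 125.53 / 5.5² = 65.1, rounded up to 66.
- Inflated: 66 × 1.5 × 1.2 = 118.8, so 119 per arm and 238 in total.

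The plan states 240 (120 per arm). The figure reproduces closely as a two-sample comparison of mean DBP.

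**2. Does any named analysis estimate that difference?**

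| Analysis | Outcomes named | Effect measure stated | Mean SBP or DBP named? |
|---|---|---|---|
| Chi-square, logistic regression | Medication and lifestyle factors | Unadjusted odds ratio | No |
| t / Mann-Whitney; paired t / Wilcoxon | Waist-to-hip ratio, awareness, adherence score, activity duration | None stated | No |
| GEE, time-by-intervention | None named | Adjusted odds ratio only | No |

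**3. What would a literal reading cost? (illustration)**

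Assumptions, not statements of the plan: DBP is normal in each arm, 80.9 (SD 10.9) and 75.4 (SD 11.5) are the two arms' follow-up distributions, and the category is DBP at or above 90 mm Hg. After 20% loss, 120 × 0.8 = 96 per arm. With the design effect, 96/1.5 = 64 effective per arm.

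*Means.* z = 5.5 / (11.20 × √(2/n)).

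- n = 96: z = 3.40; power = Φ(3.40 − 1.96) = 92.5%.
- n = 64: z = 2.78; power = Φ(2.78 − 1.96) = 79%.

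*Category.*

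- P(DBP ≥ 90) = 1 − Φ(9.1/10.9) = 20.2%, and 1 − Φ(14.6/11.5) = 10.2%. The odds ratio is about 0.45.
- Mean proportion p̄ = 0.152. Null SD term: √(2 × 0.152 × 0.848) = 0.508. Alternative SD term: √(0.202 × 0.798 + 0.102 × 0.898) = 0.503.
- Power = Φ((0.0998 × √n − 1.96 × 0.508)/0.503): 49% at n = 96 and 35% at n = 64.

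| Analysed per arm | Mean difference | DBP ≥ 90 mm Hg |
|---|---|---|
| 96, no design effect | 93% | 49% |
| 96, design effect 1.5 | 79% | 35% |

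**4. Sensitivity to the cut-point**

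At 96 per arm with the design effect, power for the categorical comparison is 61% at a cut of 76, 58% at 80, 48% at 85 and 35% at 90 mm Hg. All are below 79%, but the gap varies widely.

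The power for means is for a two-group comparison at one time point, as in the plan's sizing. Power for the time-by-intervention term also depends on the correlation between a person's two readings, which the article does not give.

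**The case against.** **A mean comparison is not ruled out.** A reader might infer that blood pressure has no possible analysis as a mean, or that it will be cut at 140/90. The article supports neither. A general sentence in Statistical Analysis says the outcome variables will be compared between and within groups, and its wording is open-ended. The list of continuous outcomes may not be exhaustive: waist circumference is measured at both surveys and is not listed either. Table 1 does not force a category, since waist-to-hip ratio is defined there by a cutoff and yet analysed as continuous. The 140/90 definition appears with the conceptual framework, and nowhere is the GEE said to use it. All of this stands. What remains is that no analysis names mean blood pressure, and the one effect measure given for the effectiveness model does not suit it.

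**Link functions belong in an analysis plan.** This is fair for an omission. Here the article does state the effect measure, without restriction to binary outcomes, so the problem is a stated rule that misfits. A GEE can model a continuous response, and the model class is not at fault.

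**The adherence score shares the problem.** Only in part. It is in the continuous list and so has a mean comparison. The misfit touches it only if it is modelled by the GEE.

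**The power figures are soft.** They are. They rest on normality, on DBP alone although the article defines control on both SBP and DBP, and on an earlier trial's before-after values standing in for two arms.

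**Conclusion.** The point holds as a mismatch between what was sized and what will be reported. The trial is sized on mean DBP, blood pressure measurements are primary and control is secondary, yet the only adjusted effectiveness model is reported solely as odds ratios, and SBP and DBP are missing from the named continuous outcomes. This follows from the text and needs no power calculation.

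The size of the loss under a literal reading is illustrative: about 49% power against 93%, or 35% against 79% with the design effect, for a cut at DBP 90 mm Hg under the assumptions given. It would change with the actual baseline mean and the cut-point. The point does not show the sample size of 240 to be wrong; that figure reproduces.

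**What to change.** In Statistical Analysis:

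1. Add SBP and DBP to the continuous outcomes.
2. State that continuous outcomes in the GEE (SBP, DBP and, if modelled there, the medication adherence score) use an identity link, with the time-by-intervention effect reported as an adjusted mean difference with 95% CI, in mm Hg for blood pressure.
3. Keep the logit link and odds ratios for binary outcomes such as blood pressure control.
4. If a linear model of the follow-up value adjusted for baseline is preferred, enter baseline as a covariate only and not also as a repeated response.

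The cost is a few sentences, with no new data and no change in sample size. The article expects analysis to finish by April 2026, so the change should be dated and made before results by arm are examined. If they have already been seen, the report should say so.

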### Qualitative Phase of the Study

#### Study Design

The qualitative phase will follow the phenomenological approach to deeply understand the lived experiences of participants during the period of the intervention.

#### Sampling

For the qualitative phase of the study, a quota sampling approach will be used among the participants in the intervention group. On the basis of adherence status (ie, high or low adherence after the intervention), participants with hypertension from the intervention group will be categorized into subgroups using a checklist. Medication adherence, as well as adherence to lifestyle modifications (restriction in salt, control of processed food intake, adequate fruit and vegetable intake, and adequate physical activity), will be considered for categorizing participants as having high or low adherence. Sample selection will continue until data saturation is reached.

#### Data Collection

Face-to-face in-depth interviews will be conducted using an in-depth interview guide developed based on existing models for health care use, medication adherence, behavior adaptation, technology acceptance, and use of mHealth for adherence. The qualitative data will be captured as field notes and voice recordings. The in-depth interviews will be conducted at a location that is convenient for the participants and without the presence of any nonparticipants. The in-depth interview guide will be prepared in English, then translated into Malayalam, and then back-translated into English. All the interviews will be conducted in Malayalam (the vernacular language in the region).

#### Study Outcomes

The primary outcome is the in-depth understanding of the participants’ views on feasibility, facilitators, and challenges of the adoption of the mHealth strategy for achieving adherence.

The secondary outcomes are insights into the facilitators and challenges of adherence to medication and a healthy lifestyle.

